 **H3.**
*IST is perceived as technically simple by older adults.*

 **H4.**
*The response to IST is modulated by genetic factors associated with muscle type, inflammation, tissue regeneration and energy metabolism.*

## 2. Methodology

### 2.1. Design of the Intervention Study

This non-randomised, single-group, pre-post-intervention, exploratory trial will evaluate the impact of IST on sarcopenia and dynapenia in adults over 70 years of age across a 16-week period. A detailed timeline of enrolment, interventions, and assessments is presented in Table 1. Each participant will act as their own control, comparing their baseline and post-intervention status. A concurrent comparison group will not be included in this phase, which will focus on feasibility and preliminary effects (see Section 4 for a discussion of limitations). Allocation to different intervention groups is not applicable. The study aims to measure the effectiveness of IST in improving muscle mass, strength and quality of life, as well as its practical applicability. Participants will be recruited in Vitoria (Alava) and Zamudio (Bizkaia, Spain) through Baigene S.L., the Judizmendi Civic Centre (Vitoria-Gasteiz City Council) and the Estadio Vital Fundazioa Foundation.

**Table 1 healthcare-13-01573-t001:** Timeline for Study Participation.

Study Phase	Main Activities	Approximate Timing
Recruitment	Identification of potential participants, initial contact through the collaborating organisations (BAIGENE S.L., Judizmendi Civic Centre, Fundación Estadio Vital Fundazioa).	Prior to the start of the study
	1st Meeting (Information and Consent): Detailed explanation of the study, objectives, exercises; signing of the informed consent form.	Approx. 2–3 weeks before baseline assessment
	2nd Meeting (Criteria Evaluation): Questionnaire (sociodemographic, habits, pathologies, medication); Comprehensive Geriatric Assessment (CGA); Review of analytical data; Anthropometric measurements and Body Composition (height, weight, BMI, InBody for SMM/ASMM); Diagnostic tests for sarcopenia (gait speed, grip strength, and confirmation of low muscle mass with ASMM/ASMI) according to EWGSOP criteria.	Approx. 1–2 weeks before baseline assessment
Baseline Assessment	(Pre-Intervention Assessment): Measurement of physiological variables (BP, HR, SpO2), functional capacity (MVIC of 8 muscle groups, static posture), quality of life (EQ-5D-5L), saliva sampling for genetic analysis.	Week 0 (one week before the start of the IST)
Intervention	IST Programme: 2 sessions/week, 30 min/session, supervised. Progression according to Table 2	Weeks 1 to 16
	Continuous monitoring: Record of attendance, protocol compliance, adverse events (see Section 2.4.3), medication and lifestyle changes (see Section 2.1.3).	Weeks 1 to 16
Final Evaluation	(Post-Intervention Evaluation): Repetition of all baseline measurements (except genetic analysis), repetition of sarcopenia diagnostic tests to assess changes; applicability questionnaires (safety, acceptability, difficulty).	Week 17 (one week after the end of the 16-week IST)
Closing of the Study	Final data analysis, preparation of reports and scientific publications.	After Week 17

**Table 2 healthcare-13-01573-t002:** The 16-week IST protocol.

Weeks	Total Working Time	Part 1		Part 2		Part 3	
		Time	%MVIC	Time	%MVIC	Time	%ME
1–4	45″	15″	20	15″	40	15″	100
5–8	60″	20″	22	20″	42	20″	100
9–12	75″	25″	24	25″	44	25″	100
13–16	90″	30″	26	30″	46	30″	100

#### 2.1.1. Criteria for Inclusion/Exclusion in Research

##### Sampling Method

Consecutive non-probabilistic sampling will be used. All individuals identified through the collaborating organisations who meet the eligibility criteria will be invited to participate until the target sample size (N = 18) is reached.

##### Recruitment Strategies

In order to reach the sample size, we will partner with BAIGENE S.L. (Vitoria and Zamudio), the Judizmendi Civic Centre (Vitoria-Gasteiz City Council) and the Estadio Vital Fundazioa Foundation. Strategies include initial contact through their services and databases (having obtained the necessary authorisations), information material in their facilities and informative talks. The potential benefits of participation will be explained, and recruitment will be continuously monitored.

The recruitment scheme was structured into two stages and led by the principal investigator and the medical doctor in the research team in order to ensure rigorous selection:

##### Stage One: Information and Consent

In the initial meeting, the principal investigator or a trained member of the team will explain the study in detail (objectives, exercises), ensuring that the voluntary nature and expectations of the study are understood. Time will be allowed for questions. At the end of the meeting, stakeholders will sign an informed consent form.

##### Consent for Ancillary Studies with Biological Samples

A specific, optional informed consent will also be requested, in a separate section, for the storage and future use of the participants’ biological samples (saliva DNA) and associated (coded/anonymised) genetic data in ancillary studies on sarcopenia, muscle ageing, response to exercise or other future genetic analyses. Emphasis will be placed on the voluntary nature of participation and on ensuring that it does not interfere with their involvement in the main study.

##### Stage Two: Evaluation Criteria

After signing the consent form, participants will be assessed in order to confirm their eligibility and safety. This will include:Questionnaires and Clinical Information: Data on sociodemographic variables (age, sex), toxic habits (alcohol consumption), history of previous/current pathologies (reviewed by the team doctor to identify contraindications according to the exclusion criteria) and medication consumed will be collected. A Comprehensive Geriatric Assessment (CGA) will be conducted, evaluating key domains with brief, validated instruments. These will include: functional status for basic Activities of Daily Living (ADL) using the Katz Index of Independence in ADL; nutritional status using the Mini Nutritional Assessment—Short Form (MNA-SF); cognitive function using the Mini-Cog©; and depressive symptoms by means of the 5-item or 15-item Geriatric Depression Scale (GDS-5 or GDS-15). If available, parameters of interest (e.g., complete blood count, glucose, urea, creatinine with estimated GFR, serum electrolytes, total protein, albumin, C-reactive protein (CRP), Vitamin D, lipid profile) will be extracted from recent analyses.Anthropometric Measurements and Body Composition: Height will be recorded (in metres, to the nearest 0.01 m) using a stadiometer, with the participant barefoot and in light clothing. Weight (kg) and Body Mass Index (BMI) (kg/m^2^) will be obtained directly from the InBody 230 bioimpedance analyser (Biospace Co., Ltd., Seoul, Republic of Korea). The same device will be used to determine Skeletal Muscle Mass (SMM) and Appendicular Skeletal Muscle Mass (ASMM), following the manufacturer’s recommendations. The Appendicular Skeletal Muscle Mass Index (ASMMI), calculated as ASMM (kg)/height (m)^2^, will be used as a key component for the diagnosis of sarcopenia.

##### Diagnostic Tests for Sarcopenia (According to EWGSOP Criteria)

Specific diagnostic tests based on the EWGSOP criteria [2,3] will be performed to confirm the diagnosis of sarcopenia, a fundamental inclusion requirement:Running speed: This will be measured with a Newtest Powertimer system (Model 3000). Two series of 4 m will be performed, with the best result being chosen. Inclusion criteria: <0.8 m/s.Manual grip strength: This will be obtained with a Jamar dynamometer (Model 5030 J1) following a standardised protocol [3,77]. The dominant hand (or the contralateral hand if this is not possible) shall be used, with the participant seated and their elbow at 90°. The highest value of the three measurements (1-min interval) will be recorded. Inclusion criteria: males < 30 kg; females < 20 kg.Skeletal Muscle Mass: The acquisition of Skeletal Muscle Mass (ASMM or ASMMI using InBody 230) was described in the previous section (‘Anthropometric Measurements and Body Composition’). Inclusion criteria: men < 8.31 kg/m^2^ (ASMMI); women < 6.68 kg/m^2^ (ASMMI).

##### Inclusion Criteria

Age 70 years or older.Diagnosis of sarcopenia according to EWGSOP criteria.

##### Exclusion Criteria

Inability to make autonomous decisions (e.g., inability to give valid informed consent) or to understand and consistently follow exercise instructions, due to significant cognitive impairment (assessed by Mini-Cog© and clinical judgement that precludes safe and autonomous participation) or other conditions that severely impair comprehension or communication.Presence of active, unstable or severe medical conditions that, in the judgement of the study’s doctor, restrict effective participation or significantly increase the risk of injury associated with the programme, including, but not limited to:○Cardiovascular: Conditions leading to exclusion include uncontrolled arterial hypertension, defined as a resting Systolic Blood Pressure (SBP) > 180 mmHg or a resting Diastolic Blood Pressure (DBP) > 110 mmHg. Other exclusion criteria are a recent major cardiovascular event (within the last 6 months), such as unstable angina, myocardial infarction or cardiac surgery; decompensated congestive heart failure (New York Heart Association [NYHA] Class III–IV); uncontrolled, clinically significant ventricular arrhythmias; or symptomatic severe aortic stenosis.○Neuromuscular: Advanced or rapidly progressive degenerative neuromuscular diseases (e.g., Amyotrophic Lateral Sclerosis [ALS]) that preclude safe and effective exercise performance or could be exacerbated by IST.○Musculoskeletal: Active/severe multi-joint inflammatory arthritis, recent unconsolidated fractures in involved areas, major orthopaedic surgery < 6 months that contraindicates exertion, or severe chronic musculoskeletal pain significantly exacerbated by IST despite adjustments.○Respiratory: Severe Chronic Obstructive Pulmonary Disease (COPD), defined as stage III-IV according to the Global Initiative for Chronic Obstructive Lung Disease (GOLD) guidelines, with significant limiting symptoms, or severe, poorly controlled asthma.○Other severe or unstable medical conditions: Exclusion criteria also include advanced Chronic Kidney Disease (CKD), such as patients on dialysis or those with an estimated Glomerular Filtration Rate (GFR) < 30 mL/min/1.73 m^2^ without explicit approval from their nephrologist; uncontrolled diabetes mellitus with severe acute or chronic complications (e.g., untreated proliferative retinopathy, severe peripheral neuropathy with risk of ulceration); or any other pathology deemed an absolute contraindication to participation by the study’s doctor.Inability to commit to attending at least 90% of the scheduled training sessions during the 16 weeks of the study.

#### 2.1.2. IST Programme

The IST programme is meticulously structured to ensure a gradual progression and precise application of the stimulus. Each exercise will consist of a single continuous isometric contraction per muscle group, divided into three consecutive phases of specific intensity and equal duration, with no rest in between. The total duration of this contraction per exercise will be progressively increased over the 16 weeks of the protocol: 45 s (weeks 1–4), 60 s (weeks 5–8), 75 s (weeks 9–12) and 90 s (weeks 13–16).

The internal structure of each progressive isometric contraction is defined as follows:First phase: Isometric contraction to 20% of the MVIC determined in the pre-intervention assessment (see Section 2.2.2).Second phase: Consecutive increase of the intensity to 40% of the MVIC.Third phase: Maximal isometric effort (100% ME). The durations of these three phases are identical within a full contraction and are detailed in Table 2.

The weekly progression also includes an adjustment in the intensity of the submaximal phases: the strength requirement (% MVIC) in the first two phases will be increased by 2% every four weeks, as detailed in Table 2. A recovery time of 1 min will be established between the end of the series of one exercise and the start of the next. This progressive design aims to ensure that participants can gradually adapt to the effort required.

The CIEX SYSTEM Isometric Force Machine (Ciex Systems©, Durango, Spain) will be used to ensure correct execution and accurate monitoring of force. It will be equipped with Chronojump force sensors (Chronojump Boscosystems^®^, Barcelona, Spain) and Chronojump software (v2.5.1-8) for real-time visualisation of the force exerted. There will be progressive intensity changes between phases. The correct position will be established individually using a HALO© digital goniometer. While performing the exercise, participants will be instructed to maintain continuous breathing and avoid prolonged Valsalva manoeuvre, thus minimising acute tension responses [78,79]. Constant supervision will allow monitoring for any signs of discomfort.

The determination of the specific angle for each exercise and participant will be individualised. This will be monitored by the qualified personal trainer or principal investigator, guided by the following principles to ensure effectiveness, safety and comfort:Assessment of Active and Comfortable Range of Motion (ROM): The participant’s active and pain-free ROM for the main joint will be assessed at the beginning of the exercise, avoiding extreme ranges that generate discomfort, pain or instability, considering their ‘specific motor restrictions’.Selection of the Intermediate Angle within the Safe Range: An intermediate angle within the comfortable ROM will be selected that seeks to avoid joint locking or excessive passive tension, and allows the participant to generate a stable and effective Maximal Voluntary Isometric Contraction (MVIC). Although the peak torque angle will not be exhaustively sought, the practitioner will guide the participant to a position in the middle zone of their safe ROM where they subjectively report that they feel comfortable exerting force, favouring optimal actin and myosin overlap.Prioritisation of Safety and Tolerability: If in doubt, the angle that warrants the greatest perceived safety and comfort will be prioritised, even if it is not the theoretically ’optimal’ angle for maximal force production.Recording and Consistency: The individualised intermediate angle, once determined and accurately measured (HALO© digital goniometer), will be recorded and used consistently across all training sessions and MVIC assessments, ensuring standardised stimulus presentation. The aim of this process is to select a joint angle that represents a significant muscular challenge and allows for high fibre activation, within a zone that is biomechanically safe, personalised and well tolerated by each older adult.

The exercises to be performed are: peck deck, pull over, lateral shoulder raise, leg extension, leg curl, lumbar, hip abduction and hip adduction. A visual demonstration of these exercises is shown in Figure 1. The detailed standards for their application (positioning, main muscles, individualised determination of angles, instructions for the three contraction phases and monitoring points) are presented in Table 3.

##### Adherence to and Compliance with the Protocol

To promote adherence to the protocol and facilitate compliance, the following measures will be implemented:Each participant will attend individually, with a pre-established, adapted timetable.The sessions will be supervised and led by a qualified personal trainer and the principal investigator, who will provide ongoing support and motivation.If a participant misses two or more consecutive excused sessions, the intervention period may be extended by up to four additional weeks to allow time for recovery.

To comply with the protocol, participants must:Complete at least 90% of the scheduled sessions.Carry out all scheduled assessments within 20 weeks.Do not make significant changes in their daily lives that could interfere with the results or safety of the study. Specifically, participants will be instructed:○To maintain their usual dietary habits and not to start any special diets or significant nutritional supplementation without consulting the research team.○To refrain from starting new intense physical exercise programmes or substantially increasing their usual physical activity beyond the IST programme.○Continue with their usual medical care and prescribed treatments, as long as they do not directly interfere with the objectives and safety of the IST (as assessed by the research team). Any relevant new medication or treatment initiated will be recorded (see Section 2.1.3).

Non-compliance with these criteria will be recorded. The criteria for discontinuation or withdrawal from the study are detailed below:

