##### Criteria for Discontinuation or Withdrawal of Participants During the Study

The IST progression protocol (Table 2) shall be applied in a standardised manner, with no individualised modifications to the progression. Persistent inability to follow the prescribed protocol, including unresolved mild discomfort, shall be managed by considering the following criteria for discontinuation or withdrawal:Voluntary withdrawal by the participant: Participants may withdraw at any time and for any reason, as informed in the consent, without penalty or impact on the participant’s medical care.Development or worsening of medical conditions: If, based on the medical judgement of the team or staff, a new condition or the worsening of a pre-existing condition contraindicates continuation with the IST or significantly increases the risk, participants may withdraw from the programme.Adverse events (AEs): Occurrence of a Serious Adverse Event (SAE) or persistent/considerable AE related to participation, which, based on the medical judgement of the principal investigator or study doctor, makes it inadvisable to continue. All these occurrences will be recorded and evaluated according to the safety protocol.Non-compliance with protocol:○Failure to complete a minimum of 90% of the sessions, even after considering the extension of the period.○Persistent inability or refusal to perform exercises according to instructions and proper technique, compromising safety or validity, despite supervision and correction.○Failure to complete scheduled assessments within 20 weeks.Significant lifestyle changes or concomitant treatments: Initiation of unrelated intense exercise, drastic unsupervised dietary changes, or medical treatments that significantly interact with outcomes or safety, as assessed by the research team.Failure to engage in follow-up sessions: If the participant becomes unresponsive and does not attend sessions/assessments, despite reasonable attempts at contact, discontinuation will be considered.

The main reason will be documented in all cases of discontinuation or withdrawal. Data collected up to that point will be securely retained and considered for inclusion in statistical analyses (e.g., intention-to-treat), as described in the ‘Statistical Analysis’ section. Participants who discontinue the intervention will be able to continue with scheduled assessments if they wish to do so, provided that this is feasible.

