#### 2.2.3. Post-Intervention Evaluation

A final assessment will be performed one week after completion of the 16-week IST programme (week 17). All baseline measurements (physiological variables, functional capacity including MVIC and posture, quality of life by EQ-5D-5L, and the components of the sarcopenia diagnosis) will be repeated to assess any changes induced by the training, with the exception of the genetic analysis, which is only performed at baseline. Additionally, applicability questionnaires (safety, acceptance and perceived difficulty using Likert scales) [87] will be administered to assess the IST protocol.

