#### 2.4.2. Interim Analyses and Trial Stopping Guidelines

No formal interim analyses of efficacy or futility are planned that would lead to early stopping of the trial. The study will continue until completion of the 17-week follow-up of all participants, unless unforeseen safety concerns warrant an overall reconsideration of the protocol by the principal investigator and the ethics committee, who would make a decision on early termination for safety reasons.

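### A fully extended participant is assessed in week 21, past the 20-week limit, and the H1 adverse-event window stops before the final assessment

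*Protocol article*

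**What the plan says.** **Timing.** Training is planned for weeks 1 to 16 at two sessions a week, with baseline in week 0, one week before training starts (Table 1). Table 1 dates the final evaluation "Week 17 (one week after the end of the 16-week IST"), and Section 2.2.3 gives the same one-week gap.

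**Extension and limit.** Under the adherence heading of Section 2.1.2, two or more excused absences in a row mean that "the intervention period may be extended by up to four additional weeks to allow time for recovery". The list that follows requires participants to "Carry out all scheduled assessments within 20 weeks", and then states: "Non-compliance with these criteria will be recorded". The discontinuation and withdrawal criteria in the same section repeat the limit, under non-compliance, as "Failure to complete scheduled assessments within 20 weeks". No start point for the 20 weeks is given.

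**Adverse events.** Table 1 dates the row "Continuous monitoring: Record of attendance, protocol compliance, adverse events" to weeks 1 to 16. Section 2.2.1 times the adverse-event outcome, which supplies data for H1, to the intervention period and adds weeks 1–16 in brackets. Section 2.2.2 describes the H1 analysis as covering 16 weeks. Section 2.4.3 has active safety monitoring for the whole study, with questions at every training session and spontaneous reports in between.

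**The concern.** Two rules in one section disagree at the edge. Section 2.1.3 offers the extension as a way to keep participants in the study, yet at its maximum it leads to a recorded deviation and a withdrawal criterion. The criterion on 90% attendance expressly takes the extension into account; the 20-week criterion does not. Staff facing such a participant would have to choose between two stated rules.

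The second point concerns which events count towards H1. Section 2.3.2 judges low risk by comparing the incidence of training-related injuries with published rates. The events are collected throughout, but the outcome is defined over a shorter period than the collection. Whether an injury during the repeat maximal-contraction tests, or in a make-up session, enters that incidence would depend on how the window is read.

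**Working it through.** **Inputs.** Planned training 16 weeks; extension k = 0 to 4 weeks (Section 2.1.2); final assessment one week after training ends (Table 1, Section 2.2.3); baseline one week before training (Table 1); limit 20 weeks = 140 days (Section 2.1.2). The spacing of the two weekly sessions is not stated. Call it g days, and take g between 1 and 6 as an assumption.

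**Formulas.**
- Assessment week = 16 + k + 1.
- Days from first session to assessment = 7 × (15 + k) + g + 7 = 112 + 7k + g, if the last session is the second one of its week.
- Days from baseline visit to assessment = that figure + 7 = 119 + 7k + g.

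**The plan's own figure.** k = 0 gives 16 + 0 + 1 = week 17, as stated.

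| Extension k | Assessment week | Days from first session | Days from baseline visit |
|---|---|---|---|
| 0 | 17 | 112 + g | 119 + g |
| 1 | 18 | 119 + g | 126 + g |
| 2 | 19 | 126 + g | 133 + g |
| 3 | 20 | 133 + g | 140 + g |
| 4 | 21 | 140 + g | 147 + g |

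**Against the limit.**
- By week number, only k = 4 breaches it (21 > 20).
- In days from the first session, only k = 4 breaches it, by g days. With g = 3 this is 143 / 7 = 20.4 weeks. If the last extension week holds only one session, on the weekday of the first, then g = 0 and the limit is just met.
- In days from the baseline visit, k = 4 overruns by 7 + g days and k = 3 by g days (g = 3: 143 / 7 = 20.4 weeks). A two-week extension is then the longest in whole weeks that fits.

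**Adverse-event window.** Two readings of the weeks 1–16 wording:
- *The window moves with the intervention period.* Extension sessions are inside. The week from the last session to the final assessment is outside for every participant, and the assessment repeats the maximal-contraction tests (Section 2.2.3).
- *Calendar weeks 1 to 16, read literally.* The time outside is k + 1 weeks: 1 week without an extension, rising to 5 weeks with the full extension, of which 4 are training weeks.

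With 18 participants, one injured participant left out changes the incidence by 1 / 18 = 5.6 percentage points.

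**The case against.** On the limit, the two rules can both be obeyed. The extension is discretionary and its four weeks are a ceiling, whereas the 20-week limit is mandatory, so the team could simply grant less. The timing column of Table 1 is headed as approximate, and counted from the first session the overrun is only a few days. A participant assessed in week 21 has no training left to discontinue. All of this limits the consequence. It does not remove the conflict: the text permits four weeks without reservation, Section 2.2.3 states the one-week gap without calling it approximate, and the 20-week criterion makes no exception.

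On adverse events, Section 2.2.1 uses the term intervention period, which is what Section 2.1.2 allows to be extended, so the window may well be meant to move with it. The H1 analysis in Section 2.3.2 names no window, and Section 2.2.2 refers to the procedures of Section 2.4.3, which cover the whole study. That largely answers the point about extension sessions, which fall outside only on the literal reading. It does not cover the time from the last session to the final assessment, which lies after the intervention period on either reading.

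A reader might infer that adverse events after week 16 go unrecorded. Section 2.4.3 contradicts that: the gap is in the outcome definition, not in collection.

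**Conclusion.** The point holds, and it is minor. With the full permitted extension the final assessment falls in week 21 and meets the 20-week non-compliance and withdrawal criterion. Whether a three-week extension also overruns depends on the undefined start: it does when counted in days from the baseline visit, and does not when counted from the first session or by week number. The H1 window certainly leaves out the time from the last session to the final assessment for every participant; it leaves out extension sessions only if weeks 1–16 is taken literally.

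Three stronger readings are tempting but unsupported:
- *Such participants are withdrawn and lost to the analysis.* Section 2.1.2 only has withdrawal considered and keeps the data, and Section 2.1.3 encourages the final assessment. The per-protocol set in Section 2.3 depends on attendance alone, and neither it nor the intention-to-treat analysis refers to the 20-week rule.
- *Every extension is in conflict.* One or two weeks fit from each start point considered.
- *The missing week could reverse the H1 conclusion.* Section 2.3.2 sets no numerical injury threshold, so the 5.6-point shift shows only how sensitive a proportion from 18 people is.

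The verdict rests on the one-week gap being kept and, for the counts in days, on two sessions in the last training week. That full extensions will be rare is a judgement; the protocol gives no figure.

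**What to change.** 1. In Section 2.1.2 (both places), count the assessment limit from the first training session and set it to at least 21 weeks. That is 147 days against 140 + g, so the full extension fits. Alternatively, keep 20 weeks from that same start and cap the extension at three weeks (133 + g against 140 days). The cap does not work if the 20 weeks run from the baseline visit.
2. In Table 1 and Section 2.2.3, place the final assessment one week after the participant's last training session, with week 17 as the date when there is no extension.
3. In Table 1 and Sections 2.2.1 and 2.2.2, define the H1 adverse-event window as first training session to final assessment, including any extension weeks and the repeat maximal-contraction tests.

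The cost is wording only: no added visits, participants or data, since Section 2.4.3 already collects the events. The one downside is that the H1 adverse-event count may be slightly higher.
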